# **４．****Objectives of the Clinical Study**

To verify, through a randomized controlled trial, that the conventional, low-cost suture-anchor method does not show inferior efficacy or safety compared to the mini-plate method—a double-door laminectomy using plates, which is becoming one of the current standard procedures—in patients with DCM requiring cervical laminoplasty.

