**7.1.4　Regarding Treatment Changes**

<When the Assigned Enlarged Laminar Retention Method Could Not Be Performed>

If the enlarged laminar retention method assigned at registration (mini-plate or suture-anchor) could not be performed for any reason, the attending surgeon shall perform dural decompression using the method they deem best. Prioritize the safety of the study subject and improvement of myelopathy, making appropriate judgments.

The reason the assigned laminoplasty with laminar fixation could not be performed and the laminoplasty with laminar fixation method actually performed must be entered in the case report form.

<If transitioning to posterior or anterior fusion>

If the attending surgeon determines significant cervical instability exists during surgery, or if it is deemed necessary to address intraoperative complications (e.g., laminar fracture, vertebral fracture), transition from laminoplasty to cervical posterior or anterior fusion. Prioritize the safety of the study subject, improvement of myelopathy, and spinal stability, making appropriate judgments.

- If transition to cervical fusion surgery occurs because laminoplasty was impossible, or if transition to cervical fusion surgery occurs before performing laminoplasty, the reasons must be documented in the case report form.
- For the patient in question, the study is discontinued (see 7.6), and surgery for DCM is performed using the settings and methods the surgical team deems optimal.

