**8.1.2　Secondary endpoint**

(1) Operative time

(2) Estimated blood loss

(3) Proportion achieving the MCID for recovery in cervical JOA score at postoperative 1 and 2 years

(4) Health-related QOL (EQ-5D) at postoperative 1 and 2 years

(5) Severity of neck pain, upper limb pain, and upper limb numbness (VAS) at postoperative 1 and 2 years

(6) NDI at postoperative 1 and 2 years compared to preoperative

(7) Retention rate of expanded lamina at postoperative 1 and 2 years ^3)^

(8) Proportion of hinge fractures at postoperative 1 and 2 years

(9) Percentage of gutter bone union at postoperative 1 and 2 years^4)^

(10) Cervical spine alignment at 1 and 2 years post-surgery (C-SVA, C2-7 angle, C7 slope)

(11) Paraspinal muscle cross-sectional area (C4/5 level) at postoperative 1 and 2 years

(12) Dural sac area (C3/4, C4/5, C5/6, C6/7 levels) at postoperative 1 and 2 years

(13) Grading of the mass posterior to the dural sac at postoperative 1 and 2 years

(14) Incremental Cost-Effectiveness Ratio (ICER)

(15) Surgical Complication Rates

・Intraoperative complication rate (from start of surgery to completion/closure)

・Early postoperative complication rate (from completion/closure to within 30 days postoperatively)

・Late postoperative complication rate (from postoperative day 31 to within 2 years)

・Mortality rate (entire period: includes non-surgery-related deaths)

・Reoperation rate within 2 years

*For evaluating intraoperative/postoperative complications, use the evaluation criteria from the Japanese Society for Spine Surgery and Related Research database (JSSR-DB) (<https://ssl.jssr.gr.jp/db/>).

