**・Intraoperative complication rate**

[Definition]

Report complications occurring from the start of surgery to its completion (wound closure), using the study population as the denominator. As complications of particular focus, extract the complications listed below (Table A) according to the registration items of the Japanese Spine Society Registry (JSSR-DB: https://ssl.jssr.gr.jp/db/) and report their frequency and rates.

When a complication occurs, the following details must be documented in the medical record and case report: complication name, outcome, management approach, severity, relationship to cervical spine surgery, treatment details/date of treatment, and whether hospitalization was prolonged.

Table A: Intraoperative Complications Requiring Special Attention

| **Complication** | **Management** |
| --- | --- |
| Dural tear | Primary repair, fibrin glue, artificial dura, fat grafting, spinal drainage, other |
| Massive bleeding (2000ml or more) | Allogeneic blood transfusion, autologous blood transfusion, intraoperative blood recovery, observation, other |
| Nerve Injury (Spinal Cord)/Nerve Injury (Nerve Root) | Steroid administration, observation, laminectomy, etc., other |
| Major Vessel Injury/Vertebral Artery Injury/Other Arterial Injury | Pressure hemostasis only, suturing by relevant department, specialist (vascular surgery, etc.) intervention, catheter, other |
| Vertebral body injury/Transverse process fracture | Implant addition/replacement, Other |
| Misidentification of level | Surgery performed on incorrect upper vertebra(e), Surgery performed on incorrect lower vertebra(e), Other |
| Change to conventional method | Conventional method (Kirita-Miyazaki method): (Level changed), Laminectomy: (Level changed), Other |

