**10.1.2　Safety Analysis Set (SAS)**

This is defined as the population of all cases enrolled and randomized in this study who underwent the protocol treatment (cervical laminoplasty).

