For FAS subjects, perform analyses similar to those for primary endpoints on the change in each evaluation item from preoperatively to 1 year postoperatively.

Additionally, perform analyses similar to those for secondary endpoint (2) on the change in each evaluation item from preoperatively to 1 and 2 years postoperatively.

(11) Paraspinal muscle cross-sectional area (C4/5 level) at postoperative 1 and 2 years

For FAS, perform the same analysis as for primary endpoints on the change in paraspinal muscle cross-sectional area from preoperatively to 1 year postoperatively.

Additionally, perform the same analysis as for secondary endpoint (2) on the change in paraspinal muscle cross-sectional area from preoperatively to 1 and 2 years postoperatively.

(12) Dural sac cross-sectional area (C3/4, C4/5, C5/6, C6/7 levels) at postoperative 1 and 2 years

For FAS subjects, perform the same analysis as for the primary endpoint on the change in dural canal area from preoperative to 1-year and 2-year postoperative time points.

Additionally, perform the same analysis as for secondary endpoint (2) on the change in dural canal area from preoperative to 1-year and 2-year postoperative time points.

(13) Grading of the mass posterior to the dural sac at postoperative 1 and 2 years

For FAS subjects, classify posterior spinal canal compression at 1 and 2 years postoperatively into mild (Grade 1-3) and severe (Grade 4-5). Calculate the proportion of severe posterior spinal canal compression at 1 and 2 years postoperatively by group. For between-group comparisons, calculate the difference in the proportion for each evaluation item and its 95% confidence interval, then perform Fisher's exact test. Use the Clopper-Pearson method to calculate the confidence interval.

(14) Incremental Cost-Effectiveness Ratio (ICER)

Calculate the ICER of the test treatment group relative to the control group.

Refer to Section 8.1.2 for details on the calculation method.

(15) Surgical complication incidence

For SAS, calculate the number of cases and rates of each complication by the following categories for each assigned group.

・Intraoperative complication rate (from start of surgery to end of surgery (wound closure))

・Early postoperative complication rate (from end of surgery (wound closure) to within 30 days postoperatively)

・Late postoperative complication rate (from postoperative day 31 to within 2 years postoperatively)

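### The safety set drops operations changed away from laminoplasty, and the promised non-inferior safety has neither a margin nor a between-group estimate of complications

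*Protocol*

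**What the plan says.** - **Objective.** Protocol section 4 sets out to verify that the suture-anchor method "does not show inferior efficacy or safety compared to the mini-plate method". Section 3.3 makes the same claim of non-inferiority for efficacy and safety together.
- **Safety set.** Section 10.1.2 takes "all cases enrolled and randomized in this study who underwent the protocol treatment (cervical laminoplasty"), and section 10.5 assigns all safety analyses to this set.
- **Complication analysis.** Section 10.5.3 (15): "For SAS, calculate the number of cases and rates of each complication by the following categories for each assigned group". Three windows follow: intraoperative, early and late. No difference, interval or test is named.
- **Foreseen changes of operation.** Section 7.1.4 provides for "transition from laminoplasty to cervical posterior or anterior fusion" when there is marked instability or when an intraoperative complication such as a fracture calls for it. One case it describes is: "If transition to cervical fusion surgery occurs because laminoplasty was impossible, or if transition to cervical fusion surgery occurs before performing laminoplasty". For that patient the study is discontinued, and 7.6 criterion 4 says the same.
- **Table A in 8.2.** The intraoperative complications of special interest include "Change to conventional method", with laminectomy among the entries. The denominator named there is the study population. For the early and late windows it is the analysis population.
- **Components of the endpoint.** Section 8.1.2 (15) also lists the reoperation rate within 2 years and "Mortality rate (entire period: includes non-surgery-related deaths"). Neither appears in 10.5.3 (15).

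**The concern.** A safety set should keep everyone exposed to the operation. This one depends on how the operation ended. A patient may be opened, suffer a fracture and be fused instead of receiving laminoplasty. That patient was randomised and operated on and had an event of the kind the table is meant to report, but is not in the set on which the table is built. If such changes are more frequent in one arm, that arm looks safer because of them.

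Separately, the protocol promises a conclusion on safety that its analysis cannot deliver. Non-inferiority needs an estimate of the difference and a limit to compare it with. For complications there is neither.

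**Working it through.** **1. Who is in the safety set, applying 10.1.2 to the situations in 7.1.4, 7.6 and Table A**

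| Situation | Laminoplasty performed? | In the set? |
| --- | --- | --- |
| Plate used instead of anchor, or the reverse | yes | yes, under the assigned arm |
| Method changed at some levels only | yes, at the others | yes |
| Fusion added after a completed laminoplasty (7.6 criterion 5) | yes | yes |
| Fusion instead of laminoplasty (7.6 criterion 4) | no | no |
| Full laminectomy instead of laminoplasty | no, if laminectomy is not counted as laminoplasty | no |

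The last two rows are the problem. Table A counts a change of method as a complication over the study population, while 10.5.3 counts over a set that a full change leaves. The two sections cannot both be followed for these patients.

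**2. Which endpoints get a between-group comparison in 10.5.3**

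- Items (3), (8), (9) and (13), all proportions: difference, 95% interval and Fisher's exact test.
- Item (7), retention rate: analysed like the primary endpoint, so with a difference and 95% interval.
- Item (15), complications: counts and rates per arm only.

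The only non-inferiority limit is in 10.5.2: -20% on the JOA recovery rate.

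**3. What the sample size was built for**

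Inputs from 10.2: SD 40, margin 20, one-sided alpha 0.025, power 0.9. A true difference of 0 is assumed, because none is stated.

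- Normal formula: n per arm = 2 × (1.960 + 1.282)² × 40² / 20² = 84.1, so 85 (170 in total).
- With the t distribution, power is 0.8999 at 85 per arm and 0.903 at 86. This gives 86 per arm, or 172, as stated.
- Dropout: 86 / 0.8 = 107.5, so 108 per arm, or 216, as stated.

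The figure reproduces, and it rests on the JOA score alone.

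**4. Precision available for complications**

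The protocol gives no complication rates; 5% and 10%, equal in both arms, are assumed.

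- Wald half-width at 108 per arm = 1.96 × √(2p(1-p)/108): 5.8 points at p = 0.05 and 8.0 points at p = 0.10.
- Newcombe interval: ±6.3 points with 5/108 per arm and ±8.4 points with 11/108.
- At 86 per arm, if planned dropout thins the late window: ±7.3 points with 4/86 and ±9.6 points with 9/86.

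For illustration, with an assumed safety margin of 10 points the power at 108 per arm would be 92% at a 5% rate and 69% at 10%. With a 5-point margin it would be 39% and 23%.

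**5. Effect of dropping converted patients**

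Assume 11/108 with a complication in each arm, so a true difference of 0.

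- One converted patient with a counted complication removed: 10/107 = 9.3% against 11/108 = 10.2%, a shift of -0.8 points.
- Five such patients removed: 6/103 = 5.8%, a shift of -4.4 points (Newcombe 95% interval -12.2 to 3.3).
- One converted patient without a counted complication removed: 11/107 = 10.3%, a shift of +0.1 points.

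The number of conversions is an assumption in each line.

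**The case against.** Section 10 calls itself an overview and leaves detail to a separate analysis plan, which could add intervals and further tables. That disposes of any complaint about missing layouts. It does not dispose of the set definition, which the protocol fixes in words, or of an objective without a criterion.

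The events are not lost to the trial. They are recorded as adverse events (9.1), reported if serious (9.3.2), monitored by group (12.1) and followed after discontinuation (7.6). That is true, but the planned comparison of complications still omits them.

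Safety is not wholly without comparison. Section 5.1 labels retention rate and hinge fracture as safety measures, and both are compared between arms. This stands. But they are imaging findings, analysed in the full analysis set, which also requires laminoplasty, and they have no margin.

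A reader might infer several stronger things that the protocol does not support:

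- *That tabulating by assigned arm misattributes device harms.* Analysis by assigned arm is legitimate, the fixation used is recorded (7.1.4, 7.2.2), malfunctions are recorded for each device (9.1), and reclosure is not in Tables A to D at all.
- *That every patient converted after a fracture is lost.* Fusion added after a completed laminoplasty stays in the set.
- *That mortality and reoperation were forgotten.* Section 8.2 says they are recorded independently of the complications, and 7.2.2 collects them. What is missing is one line of analysis.

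**Conclusion.** The point holds in two parts.

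First, the safety set excludes patients whose operation was changed to fusion or full laminectomy instead of laminoplasty. This conflicts with Table A and its denominator, and it can bias the comparison in favour of the arm with more such changes. On the assumed 11 of 108, the shift is about 0.8 points for each dropped patient who had a counted event. It is negligible, and in the other direction, for a patient who had none. How many there will be is unknown and may be few.

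Second, non-inferior safety is promised without a margin and without a difference for complications. With equal rates, the trial could estimate that difference to about ±6 points at 5% and ±8 points at 10%. It would be tempting to say that a doubling of complications could never be excluded. That is so at 5%, where doubling adds 5 points, but not at 10%, where it adds 10.

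The exclusion of full laminectomy rests on reading it as distinct from laminoplasty, which the protocol does not spell out.

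**What to change.** - **10.1.2:** define the safety set as all randomised patients in whom surgery was started, including those changed to another operation, analysed in the assigned arm.
- **8.2:** use this set as the denominator in all three complication windows, replacing the two differing terms.
- **10.5.3 (15):** add a risk difference with a 95% interval for each window, and for the mortality and 2-year reoperation components of 8.1.2 (15). Use an interval made for a difference of two proportions, such as Newcombe's.
- **3.3 and 4, and the same claim in sections 1, 3.4 and 5.1:** restate the aim as non-inferior efficacy, with safety described and estimated.
- **Optional:** a supplementary table by fixation actually used.

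No new data are needed. The method used and any transition to fusion are already in the surgical information, and death and reoperation are in the outcome investigation (7.2.2). The 30-day and 2-year event data of patients discontinued under 7.6 should be kept for the table where consent allows. The cost is wording, a few table lines and a more modest safety claim that the trial can support.

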**10.5.4　Subgroup Analysis**

Subgroup analyses will be performed based on the factors listed below. These analyses are not designed to ensure sufficient power and will not include multiple testing adjustments; therefore, the results of each subgroup analysis should be interpreted as exploratory findings only. Additionally, subgroup analyses related to other clinical-pathological characteristics or prognostic factors expected to have clinical significance at the time of analysis will be performed.

<Factors Planned for Subgroup Analysis>

・ Age (64 years or younger / 65-74 years / 75 years or older)

・ Gender (Male / Female)

・ BMI (≤25 / >25)

・ Preoperative Diagnosis (CSM / OPLL)

・ Number of Expanded Laminas (2 / 3 / 4)

・ Posterior spinal canal compression classification (Grade 1-3 / Grade 4-5)

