**２）Secondary Endpoints**

1) Operative time

2) Estimated blood loss

3) Proportion achieving the minimal clinically important difference (MCID) in cervical JOA score recovery rate at postoperative 1 and 2 years

4) Health-related QOL (EQ-5D) at postoperative 1 and 2 years

5) Severity of neck pain, upper limb pain, and upper limb numbness (VAS) at postoperative 1 and 2 years

6) Neck disability index (NDI) at postoperative 1 and 2 years compared to preoperative

7) Retention rate of enlarged lamina at postoperative 1 and 2 years (Retention rate)

8) Percentage of hinge fractures at postoperative 1 and 2 years

9) Percentage of bone union of gutter at postoperative 1 and 2 years

10) Sagittal alignment of cervical spine at postoperative 1 and 2 years (C-SVA, C2-7 angle, T1 slope)

11) Paraspinal muscle cross-sectional area (C4/5 level) at postoperative 1 and 2 years

12) Dural sac cross-sectional area (C3/4, C4/5, C5/6, C6/7 levels) at postoperative 1 and 2 years

13) Grading of the mass posterior to the dural sac at postoperative 1 and 2 years

14) Incremental Cost-Effectiveness Ratio (ICER)

15) Surgical complication incidence

[Rationale]

(1)(2) The Clinical Question (CQ) that led to this study's design is: “While the plate method is a simple surgical technique, it is expensive. Could the less expensive conventional method (suture-anchor) be equally effective and safe compared to the mini-plate?” Since the simplicity of a surgical technique can be measured by operating time and blood loss, these were set as secondary endpoints as direct measures to answer the CQ.

(3) In recent years, evaluating treatment effectiveness has commonly involved not only simple comparisons using patient-reported outcome measures but also assessment via the MCID (Minimal Clinically Important Difference). If treatment yields a change exceeding the MCID threshold, the treatment is considered effective. The MCID for recovery in the JOA score in compressive myelopathy has been reported as 52.8%^19)^. As secondary endpoints, comparisons between treatment groups at 1 and 2 years will be made not only for the direct intergroup comparison of recovery rates but also for the proportion achieving the MCID.

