(4) ～(6)　The JOA score is a physician-led assessment of spinal cord symptoms originating from the cervical spine. Patient-reported outcomes such as EQ-5D, VAS, and NDI were set as secondary endpoints. Furthermore, EQ-5D will also be used as the utility value when calculating the incremental cost-effectiveness ratio.

(7) For safety assessment, the retention rate^7)^ (Figure 4), an objective indicator for enlarged lamina reclosure, was set as a secondary endpoint.

[figure not shown]

(8) As a safety endpoint, the proportion of hinge fractures in enlarged laminar segments on CT^8)^ was set as a secondary endpoint.

(9) As an endpoint for surgical goal achievement, the proportion of hinge fractures showing bone union on CT was set as a secondary endpoint.

(10) Postoperative cervical kyphotic deformity is a morphological change that leads to recurrence of spinal cord symptoms and poor outcomes in cervical laminoplasty^7-9)^. As indicators of kyphotic deformity, the C2-7 lordotic angle and C-SVA were set as secondary endpoints, along with the C7 slope as a factor influencing these (Figure 5).

[figure not shown]

(11) Reduction in the cross-sectional area of the paraspinal muscles (Fig. 6), which are cervical extensors, has been reported as a factor influencing occipital pain^20)^ and as a factor involved in post-laminoplasty reclosure^7)^. Therefore, the postoperative paraspinal muscle area at the C4-5 level was set as a secondary endpoint.

[figure not shown]

(12)(13) Post-laminectomy membrane, caused by posterior dural scarring after laminectomy, is considered a factor in spinal cord re-compression^21)^. However, its incidence rate across different laminoplasty techniques remains unclear. Postoperative dural canal area and the Grading of the mass posterior to the dural sac ^22)^ (Figure 7) were set as secondary endpoints to evaluate spinal cord re-compression.

[figure not shown]

(14) A key objective of this study is to demonstrate that the experimental treatment (suture- anchor) is non-inferior in efficacy and safety to the control treatment (mini-plate), while being less expensive and offering superior cost-effectiveness. As an indicator for comparing the cost-effectiveness between the experimental and control groups, the commonly used measure, ICER, was set as a secondary endpoint.

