| Early Postoperative Complications/Adverse Events (within 30 days postoperatively) | | Confirm the presence of adverse events through medical history and physical examination.  If an adverse event occurs, document the event name, onset time, outcome, severity (including whether reoperation was required), relationship to cervical spine surgery, treatment details/date of treatment, and whether hospitalization was extended. | |
| Medical History/Physical Examination | | Conduct medical history and physical examination during regular postoperative outpatient visits. | |
| Plain X-ray | | Cervical spine (AP/Lateral/Anterior flexion lateral/Posterior flexion lateral): Confirm C2-7 angle/C-SVA/C7 slope  Full spine standing (AP/Lateral): Confirm SVA/Lumbar lordosis angle/Thoracic kyphosis angle/Pelvic incidence, check for existing vertebral fractures | |
| Cervical Plain CT | | Horizontal, sagittal, and coronal slices at each intervertebral level: Confirm presence of OPLL/Lamina retention rate, hinge fractures/gutter bone union. | |
| Cervical Plain MRI | | T2 and T1 sagittal/horizontal images  Preoperative: Maximum stenosis level, presence of intramedullary signal changes, C4/5 paraspinal muscle area, dural sac area  Postoperative: C4/5 paraspinal muscle area, dural sac area, Grading of the mass posterior to the dural sac | |
| Late Postoperative Complications/Adverse Events (From 31 days post-op to within 2 years post-op) | | If an adverse event occurs, document: event name, onset timing, severity, outcome, seriousness (whether reoperation required), relationship to cervical spine surgery, treatment details/date, and hospitalization status. | |
| Outcome Investigation | | Survival (Last confirmed survival date, presence/absence of death, date of death, cause of death)  Reoperation (Reoperation presence/absence, reoperation date, reason for reoperation, reoperation method)  Study Discontinuation (Discontinuation presence/absence, discontinuation date, reason for discontinuation) | |
| Direct Medical Costs | | Hospitalization Costs (Medical fees excluding surgery, surgery-related costs [surgery, surgical drugs, anesthesia, anesthetic drugs])  Outpatient Costs (Consultations, tests, drugs, other)  Hospitalization Re-treatment Costs for Adverse Events (Hospitalization medical fees excluding surgery, surgery-related costs [surgery, surgical drugs, anesthesia, anesthetic drugs])  Research collaborators collect the above costs from medical claims. | |

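### One planned subgroup factor, the posterior compression grade, is a postoperative secondary outcome, so arm comparisons within it are not randomised comparisons and can be biased

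*Protocol*

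**What the plan says.** Section 10.5.4 names six subgroup factors. Age, gender, BMI and preoperative diagnosis are known before randomisation. The other two are "Number of Expanded Laminas (2 / 3 / 4" and "Posterior spinal canal compression classification (Grade 1-3 / Grade 4-5".

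The grade appears elsewhere only as an outcome:

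- Section 5.1 lists it as secondary endpoint 13: "Grading of the mass posterior to the dural sac at postoperative 1 and 2 years".
- Section 10.5.3 (13) compares the arms on it with the same cut, instructing the analyst to "classify posterior spinal canal compression at 1 and 2 years postoperatively into mild (Grade 1-3) and severe (Grade 4-5".
- The schedule in 7.2.1 marks it at 1 and 2 years and leaves the pre-registration column empty.
- Section 7.2.2 puts it among the later MRI readings, "Postoperative: C4/5 paraspinal muscle area, dural sac area, Grading of the mass posterior to the dural sac", and omits it from the earlier ones, "Preoperative: Maximum stenosis level, presence of intramedullary signal changes, C4/5 paraspinal muscle area, dural sac area".

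On its role, the rationale for endpoints 12 and 13 in section 5.1 says that scarring behind the dura "is considered a factor in spinal cord re-compression" and that "its incidence rate across different laminoplasty techniques remains unclear".

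Section 10.5.4 calls all subgroup results exploratory. The reasons it gives are lack of power and no multiplicity adjustment.

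**The concern.** A subgroup analysis keeps the protection of randomisation only if the subgroup is fixed before allocation, or at least cannot be changed by it. The grade is seen a year or more after surgery, and the protocol measures it because it might differ by technique. It may lie on the path from fixation method to recovery. If it does, the patients with a mild grade in one arm are no longer comparable with those in the other, and splitting by grade can take out part of the effect that the trial is looking for.

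In a non-inferiority trial, an error towards no difference is the unwelcome direction. The exploratory label warns about chance findings; it does not warn that the comparison itself may be systematically off.

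The number of expanded laminae raises a milder form of the same question. It is recorded with the surgical information, after an open allocation.

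**Working it through.** **When each factor is known.** Section 7.1.2 requires randomisation by the day before surgery, and section 5.2.1 states that the trial is not blinded.

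| Factor in 10.5.4 | Where recorded | Known before allocation? |
| --- | --- | --- |
| Age, gender, BMI, diagnosis | Patient background (7.2.2) | Yes |
| Number of expanded laminae | Surgical information (7.2.2) | Not in the recorded data; 7.1.3 implies a plan |
| Posterior compression grade | MRI at 1 and 2 years (7.2.1, 7.2.2) | No |

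**The protocol's own figure.** Section 10.2 gives a margin of 20 points, SD 40, one-sided alpha 0.025 and power 0.9. The normal formula gives n = 2 × (1.960 + 1.282)² × 40² / 20² = 84.1, so 85 per arm. With the t distribution, power is 0.8999 at 85 and 0.9032 at 86, so 86 per arm, 172 in total, as stated. Then 172 / 0.8 = 215, or 216 for equal arms. The sample size is not in dispute; it is used below for precision.

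**Illustration of the bias.** The grade rates and effects here are assumptions; none comes from the protocol. Let p be the proportion with a severe grade (4-5), L the recovery points lost with a severe grade, and d any effect of anchor against plate that does not pass through the grade. Differences are anchor minus plate.

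- Overall difference = d − L × (p_anchor − p_plate)
- Difference within each grade = d, if nothing else links grade and recovery

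With complete mediation (d = 0):

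| p plate | p anchor | L | Overall | Within each grade |
| --- | --- | --- | --- | --- |
| 10% | 35% | 40 | −40 × 0.25 = −10 | 0 |
| 20% | 50% | 40 | −40 × 0.30 = −12 | 0 |
| 10% | 60% | 50 | −50 × 0.50 = −25 | 0 |
| 20% | 20% | 30 | 0 | 0 (no bias) |

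The zeros follow from setting d = 0. They show what can happen, not what is expected.

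**With a shared cause.** Suppose an unmeasured prognostic factor is worth 15 recovery points per SD and correlates 0.5 with the latent scale behind the grade. With z_p the standard normal quantile at p and φ(z_p) the density there, its mean contribution to recovery is −0.5 × 15 × φ(z_p)/p in the severe stratum and +0.5 × 15 × φ(z_p)/(1 − p) in the mild one.

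- 20% against 50%, L = 40, overall −12. Severe: −7.5 × 0.399/0.5 + 7.5 × 0.280/0.2 = −5.98 + 10.50 = +4.5. Mild: 7.5 × 0.399/0.5 − 7.5 × 0.280/0.8 = 5.98 − 2.62 = +3.4. The sign is reversed.
- 20% against 40%, no effect on recovery, overall 0. Severe: −7.5 × 0.386/0.4 + 10.50 = +3.3. Mild: 7.5 × 0.386/0.6 − 2.62 = +2.2. A difference appears where there is none.

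Simulations of 2,000,000 patients per scenario agree to within about 0.2 points.

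**Precision.** Take 86 evaluable per arm and rates of 10% and 35%: about 9 against 30 severe and 77 against 56 mild. With SD 40 within strata, the 95% half-widths are

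- severe: 1.96 × 40 × √(1/9 + 1/30) = 29.8 points;
- mild: 1.96 × 40 × √(1/77 + 1/56) = 13.8 points.

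The severe interval is wider than the 20-point margin.

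**The case against.** The case on the other side has real weight.

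- **Bias is not certain.** It needs the arm to change the grade. Section 5.1 calls the incidence by technique unclear, and section 13.2 expects no difference in complications or safety. With equal grade rates the bias is zero. A reader might infer that the subgroup effects are biased; the documents support only that they can be.
- **Nothing decisive rests on the subgroup.** Non-inferiority is judged on the full-set ANCOVA in section 10.5.2, which does not condition on grade. Section 10.5.3 (13) compares the proportion of severe grades directly. In the illustrations, both the overall deficit and the grade imbalance would still be estimated there. The primary conclusion is not in danger.
- **Two reassuring subgroups would not follow.** It is tempting to say that both strata would look reassuring. At this sample size the severe stratum would be inconclusive; only the mild one could appear so.
- **The laminae factor is weaker.** A reader might infer that the number is settled during surgery by a surgeon who knows the arm. No section says so. Section 7.1.3 speaks of planned expansions and completes them before fixation, and the inclusion criteria require stenosis on imaging. No mechanism is given by which fixation would alter the number of levels. What remains is that the plan is not recorded before allocation, and that section 7.1.3 leaves technique other than fixation to the surgical team.
- **A separate analysis plan could relabel the grade analysis.** It could, but the protocol itself fixes the factor list, and the list is wrong on this factor.

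None of this makes the grade a baseline variable, and the exploratory caveat does not cover the problem.

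**Conclusion.** The point holds in a limited form. The posterior compression grade is an outcome measured after treatment, with no preoperative counterpart, and should not define subgroups for the treatment effect. Within-grade comparisons lose the protection of randomisation and can be biased in either direction, including towards no difference, if the fixation method affects the grade.

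The size is unknown. Under assumed grade rates, an overall deficit of 10 to 25 points could have an expected value of zero within both grades under complete mediation, and a shared unmeasured cause could add a spurious 2 to 5 points. With equal grade rates there is no bias.

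The primary non-inferiority conclusion, the endpoint 13 comparison and the sample size are unaffected. For the number of expanded laminae, influence by arm is possible but not shown.

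**What to change.** Remove the compression grade from the list in section 10.5.4 and keep it as secondary endpoint 13. If its relation to recovery is of interest, report it as a descriptive analysis, stated to be non-randomised, and say which visit's grade is used.

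For the laminae factor, enter the planned number in the EDC at registration, before allocation, and define the subgroup by that number. For patients already allocated, a plan written down afterwards would not carry the same weight.

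The cost is one line deleted, one data field added, and a protocol amendment with ethics committee review and notice to the sites under section 22.2. The sample size and the primary analysis do not change.
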